## Abstract

**Background:**

In European countries, including Switzerland, as well as in many states worldwide, cannabis is the most widely used psychoactive substance after alcohol and tobacco. Although approximately one in ten users develop serious problems of dependency, only a minority attends outpatient addiction counseling centers. The offer of a combined web-based self-help and chat counseling treatment could potentially also reach those users who hesitate to approach such treatment centers and help them to reduce their cannabis use.

**Methods/design:**

This paper presents the protocol for a three-armed randomized controlled trial that will test the effectiveness of a web-based self-help intervention in combination with, or independent of, tailored chat counseling compared to a waiting list in reducing or enabling the abstention from cannabis use in problematic users. The primary outcome will be the weekly quantity of cannabis used. Secondary outcome measures will include the number of days per week on which cannabis is used, the severity of cannabis use disorder, the severity of cannabis dependence, cannabis withdrawal symptoms, cannabis craving, the use of alcohol, tobacco, and other non-cannabis illicit drugs, changes in mental health symptoms, and treatment retention. The self-help intervention will consist of 8 modules designed to reduce cannabis use based on the principles of motivational interviewing, self-control practices, and methods of cognitive behavioral therapy. The two additional individual chat-counseling sessions in the additional chat condition will be based on the same therapy approaches and tailored to participants’ self-help information data and personal problems. The predictive validity of participants’ baseline characteristics on treatment retention and outcomes will be explored.

**Discussion:**

To the best of our knowledge, this will be the first randomized controlled trial to test the effectiveness of online self-help therapy in combination or without chat counseling in reducing or enabling the abstention from cannabis use. It will also investigate predictors of outcome and retention for these interventions. This trial is registered at Current Controlled Trials and is traceable as
ISRCTN59948178.

## Background

Cannabis is the most commonly used illicit drug in the developed world; e.g., a rough European estimate suggests that approximately 22% of Europeans within the ages of 15 and 64 have tried cannabis, and approximately 6.8% of this population report using cannabis in the past month. This represents 12 million Europeans, of whom 25% report daily cannabis use
[1]. Switzerland has the third highest national prevalence of cannabis use in Europe; the lifetime prevalence rate is 27.9% (men 32.8%, women 23.2%), and the 12-month prevalence rate is 5.1% (men 7.5%, women 2.8%)
[2]. The age group with the highest prevalence is between 15 and 24 years; this group has a 17.3% 12-month prevalence rate, and among these users nearly one fifth use cannabis daily
[2].

Despite these high numbers, only a minority of cannabis users is at risk of cannabis dependence. Currently, the estimates of the risks of cannabis dependence based on general population surveys suggest that between 10 and 11 percent of all cannabis users develop cannabis dependence
[3,4]. However, the risks of cannabis dependence
[5] and cannabis use problems
[6] are much higher among cannabis users who consumed cannabis in early life. Daily cannabis use is associated with poorer mental and physical health, lower educational achievement, and decreased cognitive functioning
[7]. Moreover, there is clear evidence from numerous studies that frequent cannabis use is strongly associated with a broad range of primary mental illnesses
[8]. Thus, specific attention should be paid to mental disorders in heavy cannabis users.

Treatment demand statistics from Swiss outpatient addiction treatment centers demonstrate a linear increase in new treatment entry cases in which cannabis is main problem substance from 2003 (12%) to 2011 (46%)
[9]. The main group of cannabis use disorder treatment seekers consists of young males between the ages of 15 and 24
[9]. In Europe, an increase in the demand for treatment in which cannabis is the main problem substance has also observed, although smaller than that in Switzerland
[10]. However, it is obvious that the majority of problematic cannabis users, of whom it is estimated that one-half develop cannabis dependence
[5] and many demonstrate co-occurring mental health problems, is still not in treatment.

There are several explanations for the low treatment attendance rate of problematic cannabis users: 1) accessibility—in many European countries and especially in rural locations, addiction treatment services are scarce, or treatment seekers are required to travel long distances to more urban areas for access to treatment. Moreover, the operating hours of addiction counseling centers are typically during office hours, which make attendance difficult for those cannabis users who have jobs and work during these hours; 2) stigmatization and need for social distance—many problematic cannabis users do not want to be stigmatized, desire personal distance from the counselor
[11], or simply want to quit on their own
[12]; and 3) the scarcity of insight into the problem affects motivation to change—many users see the risk of the development of minor mental health problems, such as mild depression symptoms, during ongoing problem cannabis use but rarely see the physical risks such as the development of COPD, lung cancer, and heart disease; this phenomenon is more apparent in frequent users than occasional users
[13,14]. Those who are aware of such physical risks from problematic cannabis use are also more ready to quit
[13]. Raising awareness of cannabis-related physical health risks might also increase intentions to reduce or quit cannabis use. In general, the principle of concurrent cover (i.e., non-invasive, low-cost interventions in which therapeutic intensity can be enhanced according to need) appears to be an appropriate mean for problematic cannabis users to lower their ever-increasing health care costs
[15], and this consideration is of interest to Switzerland and other industrialized countries suffering from exorbitant health costs.

Web-based self-help programs that reduce problematic consumption are able to facilitate access to consumer groups in the general population that do not want to be stigmatized. Such programs have consistently been shown to be effective in the reduction of problematic alcohol use
[16,17] and (although less efficiently and consistently
[17]) in tobacco smoking cessation
[18,19]. Interestingly, the availability of web-based self-help with individual chat sessions has been demonstrated to aid the reduction of alcohol use and alcohol disorder-related symptoms in problematic alcohol users
[20].

Studies of web-based programs for the reduction of the most frequently used illicit drugs, such as cannabis, cocaine and amphetamines, are scarce
[21,22]. Currently, there are only two specific web-based programs for the reduction of cannabis use that have been investigated in randomized controlled trials, and these programs employ different intervention approaches
[23,24]. The German “Quit the Shit” program
[24] is based on principles of self-regulation and self-control and is a solution-focused approach. This program is structured into weekly personalized feedback sessions based on participants’ consumption diary entries, intake and termination chats, and the total allowed program time is 50 days. Attrition in the German study of Tossmann and colleagues
[24] was high and higher in the intervention (11.6%) condition than in the waiting list control condition (24.7%). Nevertheless, these authors found significant effects on cannabis use reduction in their per-protocol and last observation carried forward analyses. The Australian program “Reduce Your Use: How to Break the Cannabis Habit”
[23] is a fully automated self-help intervention consisting of 6 modules for the amelioration of cannabis use disorders based on cognitive-behavioral therapy (CBT) approaches
[25,26], motivational interviewing (MI
[27]), and behavioral self-management (BSM
[28]). This program was tested for effectiveness in a randomized-controlled trial and compared to a psycho-educative control condition also consisting of 6 modules. Study retention was higher in the intervention and the control condition after 6 weeks (66% vs. 64%) and at a 3-month follow up (54% vs. 52%) than in the aforementioned German study
[24]. The frequency of cannabis use and the quantity of cannabis consumed were both more reduced in the intervention group than in the control group at 6 weeks and at the 3-month follow up.

The combination of a fully automated self-help intervention based on therapy approaches of the study of Rooke and colleagues
[23] with additional individual chat sessions for the reduction of cannabis use could potentially increase the effectiveness of interventions for problematic cannabis as has been demonstrated for the reduction of alcohol use in problematic alcohol users
[20]. More interactive web-based interventions may be more effective in reducing cannabis use in problematic cannabis users. However, the results of the Australian study
[23] need confirmation by other studies. Specifically, the high rates of study retention in the intervention and control groups may be due to limited geographic access of many rural users to the addiction treatment system in Australia, which did not appear to be the case in the German study, which encountered considerable retention problems
[20]. Therefore, the treatment approaches adopted for web-based self-help by Rooke and colleagues
[23] should also be validated in countries with high densities of addiction counseling services such as Switzerland.

The current study aims at to investigate and compare the effectiveness of web-based self-help interventions in combination with tailored chat counseling based on CBT, MI, and BSM in reducing cannabis use in problematic cannabis users. More specifically, this study aims to compare the effectiveness of interventions that include chat-counseling and web-based self-help, web-based self-help alone and a waiting list control condition in the reduction of cannabis use in problematic cannabis users in a three-arm randomized controlled trial.

### Study interventions

The intervention in the first arm consists of the web-based self-help intervention from study arm two in combination with two individual chat-counseling sessions based on MI and CBT approaches that are tailored to the data the participants entered into the self-help intervention and individual requests. The web-based self-help intervention “Can Reduce” from study arm two is based on classical CBT approaches for the treatment of cannabis dependence
[26], MI approaches
[27], and BSM
[28]. Study arm three consists of a classical waiting list. Figure 
1 presents a detailed overview of the aforementioned study arms.

**Figure 1 F1:**
[figure not shown]
**Trial flowchart.** This figure provides an overview of the participant flow for this trial.

Study arm one and two involve weekly reminder e-mails to login and fill out a consumption diary. The following modules, organized into three main parts, are offered as a web-based self-help intervention (study arms one and two):

• Part 1: Introduction

• Registration process

• Explanation of the cannabis consumption diary and its fully automated progress charts and statistics

• Examination of the pros and cons resulting from a change in cannabis consumption patterns and further principles of motivational interviewing to address motivation

• Explanation of the “My Can Reduce” folder (this folder allows individuals to review the acquired summarized module documents, e.g., the list of the top five strategies for dealing with cannabis cravings)

• Explanation of the emergency button for immediate responses to frequently asked questions and access to emergency contacts

• Part 2: Key Modules (participants are encouraged to complete these modules in the order presented below)

• Module 1: Strategies for goal achievement

• Module 2: Identifying risk situations

• Module 3: Dealing with cannabis craving

• Module 4: Dealing with relapses

• Part 3: Further Modules (participants are encouraged to complete at least two, in any order)

• Module 5: Tobacco smoking during the reduction of cannabis use

• Module 6: Saying “no” to foster refusal skills

• Module 7: Dealing with burdens

• Module 8: Preserving achievements

Furthermore, a glossary that explains the terms, definitions, and concepts used in the intervention, information about the history of cannabis use, the short-, medium- and long-term effects of cannabis, the physical risks of cannabis (COPD, lung cancer, cardio-vascular, etc.), co-occurring mental health problems (depression, psychosis, ADHD, etc.), and harm reduction techniques for the use of cannabis with recommendations (these recommendations favor oral intake and are based on the recommendations for medical cannabis use
[29,30]) will be provided in an appendix accessible after login, along with frequently asked questions and their corresponding answers.

The additional two chat counseling sessions in study arm one will apply support regarding behavioral change according to MI, discuss the modules of the web-based self-help part based on MI and CBT, review the development of the consumption diary and will be structured as follows:

• Chat session 1: Starting point and objective agreement

• Personalized feedback according to baseline assessment of cannabis related physical and mental health risks

• Review of successful strategies of change related to topics other than cannabis

• Imagining daily routines after cannabis cessation; exploration of aims to live without, and the dissonances of, cannabis use; mobilization of social support with the invitation for a relevant third person to join chat session 2

• Agreeing on a cannabis use objective expressed in tangible numbers (e.g., a maximum of two standard joints per week, complete cannabis abstinence etc.)

• Chat session 2: Experience exchange and consolidation

• Experience exchange regarding the agreed-upon objective since the starting point

• Review of the patterns of the consumption diary goals and achievements

• Review and consolidation of web-based self-help modules

• Experience and improvement of social support

• Revising objectives

• Saving strategies for long-term success

The web-based self-help intervention and the subsequent tailored chat counseling aim to reduce cannabis use. However, those participants who seek cannabis abstinence will also be encouraged to make step-by-step reductions until full abstinence has been reached. The maintenance of abstinence from one day to the next, as is recommended by the content of tobacco prevention websites
[31], will not be advised for safety reasons (e.g. to avoid possible severe withdrawal symptoms).

Participants randomized to the waiting list will have the opportunity to participate in the web-based self-help intervention 3 month after registration. Follow up measures for those participants will be assessed online or by telephone interviews for those participants who cannot be reached online at the 3 month follow up.

## Methods/design

### Aims of the trial

This study aims to compare the effectiveness of a web-based self-help intervention alone or combined with chat counseling in the reduction of the cannabis use of problematic cannabis users via a three-arm randomized controlled trial. The primary outcome is the weekly quantity of cannabis consumed (measured in the number of standard joints per week) at the 3-month follow up. The secondary outcome measures include the frequency of cannabis use days (7 day point prevalence of cannabis use days), changes in problematic cannabis use, severity of cannabis dependence, cannabis withdrawal symptoms, cannabis craving, the use of other psychoactive substances, mental health symptoms, functional health states, intervention satisfaction, and treatment retention. The predictive validity of participant characteristics for treatment retention and primary and secondary outcomes will be explored.

### Study population

The study population will be recruited through the Can Reduce website, several websites from local outpatient treatment centers, and from nightlife prevention websites. In addition, advertisements will be placed in internet-forums and (commuter) newspapers.

### Hypotheses

We hypothesize that web-based interventions, which are more interactive, will be more effective in reducing cannabis use among problematic cannabis users. We will test the following detailed study hypotheses with respect to the main outcome, i.e., reduction of the quantity of cannabis used between the baseline and the 3-month follow up:

1. Tailored chat-based counseling in combination with web-based self-help for the reduction of cannabis use (study arm 1) is more effective than the waiting list control condition (study arm 3).

2. Web-based self-help for the reduction of cannabis use (study arm 2) is more effective than the waiting list control condition (study arm 3).

3. Chat-based counseling in addition to web-based self-help for the reduction of cannabis use (study arm 1) is by trend more effective than web-based self-help alone (study arm 2).

Moreover, we expect the participants of study arm 1 to improve more than those in study arm 2 with respect to the secondary outcomes between the baseline and the three-month follow up termination.

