### Estimation of the expected effect sizes and sample size

Based on results of the study of Rooke and colleagues
[23], we expect small to medium effect sizes for the reduction of the quantity of cannabis used and the frequency of cannabis use between study arm 2 (web-based self-help without chat counseling) and study arm 3 (waiting list control) of at least 0.15 (Cohen’s f) between t0 and t2. Assuming that the study arm 1 (web-based self-help with chat counseling) will result in a larger Cohen’s f, we rely on the aforementioned comparison (arm 2 vs. arm 3) for sample size estimation. A sample size of n = 89 in each study group would have 80% power (F-test, α = 5%) to detect this difference based calculations performed with the G-Power software. Thus, we aim to recruit a total of 267 participants.

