## Discussion

To the best of our knowledge, this will be the first randomized controlled trial to test the effectiveness of online self-help therapy alone or in combination with chat counseling in reducing or enabling the abstention from cannabis use. This study will add to the ongoing discussion of whether web-based interventions that are more interactive are more effective in reducing substance use in problematic users
[20]. This study will also be the first to investigate predictors of outcome and retention for online self-help and for chat counseling that aim to facilitate the reduction or cessation of cannabis use. If the efficacy of this form of self-help is demonstrated in this RCT, this self-help intervention will be integrated into the basic services for cannabis users of the national addiction internet portal of Switzerland and will potentially be able to reach those cannabis users who have difficulties attending outpatient addiction treatments that follow the principle of concurrent cover
[15]. Specifically, people who rely on evening sessions after work, those in need of social distance, and those worrying about stigmatization
[11] may profit from this new addiction intervention. This intervention will foster problem insight regarding physical problems that can accompany ongoing problematic cannabis use
[13,14] utilizing a non-directive MI self-help intervention and/or chat counseling style.

Previous face-to-face therapy intervention research has demonstrated that the goal of cannabis abstinence and the desired goals regarding the reduction of cannabis use change frequently in problematic cannabis users
[46], especially in those who choose abstinence as the agreed-upon aim of therapy. Failure to reach the fixed consumption aim might result in frustration, self-deception, or in concealment of cannabis relapse from the therapist during face-to-face therapy, which may result in misleading effects. In contrast to face-to-face therapy, Can Reduce is anonymous and asks participants to re-login weekly and to set daily consumption aims week-by-week after the evaluation of past cannabis use. Moreover, the chat counseling sessions are tailored to the aims reported in the consumption diary and reported use. Thus, we expect self-deception and concealment to be less pronounced in the intervention arms.

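### Hypothesis 3 (chat plus self-help versus self-help alone) is to be tested on the main outcome but is worded *by trend*, an undefined standard, for a contrast the sample size was not set for

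*Protocol article*

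**What the plan says.** The Hypotheses section opens with a general and unqualified statement: "We hypothesize that web-based interventions, which are more interactive, will be more effective in reducing cannabis use among problematic cannabis users". It then says: "We will test the following detailed study hypotheses with respect to the main outcome", and numbers three of them. Hypotheses 1 and 2 set each active arm against the waiting list and use the plain comparative. Hypothesis 3 sets arm 1 (chat plus self-help) against arm 2 (self-help alone) and says that arm 1 "is by trend more effective than web-based self-help alone (study arm 2"). The added words appear in hypothesis 3 only.

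The aim in the Background names all three arms: "this study aims to compare the effectiveness of interventions that include chat-counseling and web-based self-help, web-based self-help alone and a waiting list control condition". The Discussion says that the study will contribute to the debate on "whether web-based interventions that are more interactive are more effective in reducing substance use in problematic users".

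The sample-size section takes an effect for arm 2 versus arm 3 "of at least 0.15 (Cohen’s f) between t0 and t2". For the chat arm it only supposes a bigger effect, without a figure, and names the contrast that sets the size: "we rely on the aforementioned comparison (arm 2 vs. arm 3) for sample size estimation". The result is 89 per arm and 267 in total, at 80% power with an F-test and α = 5%. The Data analysis section names GEE models and sets no criterion specific to hypothesis 3.

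**The concern.** Of the three contrasts, only arm 1 versus arm 2 isolates what chat adds. It is therefore the direct test of the unqualified opening hypothesis about interactivity. Yet it is the one contrast given a softer wording, and nothing in the article says what result would meet that wording or refute it. Readers commonly take a trend to mean either a difference in the expected direction or a p-value a little above 0.05. On either meaning, a result that fails the usual 5% test could be presented as confirming a pre-specified main-outcome hypothesis.

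The sizing adds to this. Assuming a larger effect for arm 1 covers arm 1 versus the waiting list. It says nothing about the size of the increment of arm 1 over arm 2. If that increment is smaller than the effect of self-help over the waiting list, a non-significant result is likely even when chat does help. An undefined standard matters most in that situation.

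**Working it through.** **Inputs from the article:** f = 0.15 for arm 2 versus arm 3; 89 per arm; α = 5%; 80% power; F-test; baseline to the 3-month follow-up (sample-size section). Allocation is 1:1:1 (Randomization and allocation). **Not given:** the correlation between repeated measures, and any effect for arm 1 versus arm 2. Both are assumed below.

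**Step 1. Reproduce 89 per arm.** Take a repeated-measures F-test with 2 groups, m = 2 time points and correlation ρ = 0:

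λ = f² × N × m / (1 − ρ), with 1 and N − 2 degrees of freedom.

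With N = 2 × 89 = 178: λ = 0.0225 × 178 × 2 = 8.01, df = 1 and 176, power = 0.804. The smallest total reaching 80% is 177 (power is 0.799 at 176), so equal arms need 178, or 89 each. The stated figure is reproduced.

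The match depends on ρ = 0. With ρ = 0.5 the same group-by-time test would need only 90 in total. A plain two-group F-test without the repeated measure has power 0.51 at 89 per arm.

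**Step 2. Apply the same model and the same 89 per arm to arm 1 versus arm 2.** Here f is the increment of chat over self-help, and λ = f² × 356.

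| Assumed increment f | λ | Power at two-sided 5% | Power if p < 0.10 sufficed | n per arm for 80% at 5% |
|---|---|---|---|---|
| 0.15 (same as self-help vs waiting list) | 8.01 | 80% | 88% | 89 |
| 0.10 (two thirds) | 3.56 | 47% | 59% | 198 |
| 0.075 (half) | 2.00 | 29% | 41% | 350 |
| 0.05 (one third) | 0.89 | 16% | 25% | 786 |

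The article expects high attrition (last paragraph of the Discussion) and the sample-size section makes no allowance for it. Losses would lower these figures.

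**Step 3. False-support rate when chat adds nothing**, for each possible meaning of *by trend*:

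- Direction only: the estimate favours chat with probability 0.50 by symmetry, so 50%.
- Two-sided p < 0.10: 10% in both directions together, 10% / 2 = 5% in chat's favour.
- Two-sided p < 0.05, for comparison: 5% / 2 = 2.5% in chat's favour.

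The article does not say which applies.

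**Step 4. What a null result would show.** For a simple comparison of two means with 89 per arm, the 95% half-width is t(0.975; 176) × √(2/89) = 1.974 × 0.150 = 0.296 SD. For two groups d = 2f, so the sizing effect f = 0.15 equals 0.30 SD. An estimate near zero would therefore argue against an increment above about 0.30 SD, but would leave smaller increments open.

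**The case against.** The strongest reply is that *by trend* is a modest expectation and not a decision rule: the authors may simply expect a small gain over an active comparator. Hypotheses 1 and 2 also carry no level or sidedness in that section, the GEE analysis sets no relaxed threshold, and the only level in the article is 5%. Levels per contrast, sidedness and testing order are commonly left to an analysis plan, which is not shown.

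Much of this stands. A reader might infer that the sponsor plans to count a non-significant difference as support, or has put a weak standard in place of power. The article says neither. It states openly which contrast set the sample size and claims no power for the other. Testing a contrast with less power than the sizing contrast is common and is not an error in itself. A fixed testing order is one option among several, so its absence is no fault.

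Three further stronger readings also fail:

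- **That chat versus no chat is the trial's single contribution.** The Discussion lists others, including the first randomised test of online self-help with or without chat and the study of predictors. Integration into the national portal is tied to the efficacy of the self-help.
- **That a null result would be uninformative.** Step 4 shows that it would still argue against increments above about 0.30 SD.
- **That power is as low as a simple t-test suggests** (10% at 0.10 SD and 26% at 0.20 SD). Those figures are arithmetically right, but that test gives only about 51% power at the sizing effect itself, so they bring in a separate question about the sample size. The model that yields 89 per arm gives 16% and 47% for the same two effects (f = 0.05 and 0.10).

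What the reply does not remove is the wording. The phrase stands inside a hypothesis that the article says will be tested, and it differs from the two beside it. A reader cannot tell what result would count against it.

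**Conclusion.** The point holds as a defect of wording, together with an undeclared limit on one contrast. Hypothesis 3 is given a standard that is defined nowhere in the article and that permits a non-significant difference to be reported as support. Depending on its meaning, the chance of false support in chat's favour is 50% or 5%, against 2.5% under an ordinary two-sided 5% test.

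The sample size was set for a different contrast. It gives about 80% power for this one only if chat adds as much over self-help as self-help adds over the waiting list, which the article does not assume. For increments of two thirds, half and one third of that size, power is 47%, 29% and 16%. These figures rest on ρ = 0, on assumed increments and on full follow-up. The estimates for hypotheses 1 and 2, the analysis model and the sample size are not called into question by this point.

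**What to change.** In the Hypotheses section, delete *by trend* and do one of the following:

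- hold hypothesis 3 to the same two-sided 5% level as the other two contrasts; or
- label arm 1 versus arm 2 a secondary estimate, reported with its 95% interval.

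In either case, add to the sample-size section that the number of participants was not set for this contrast. Add also that a result not significant at 5% will not be described as showing that chat adds benefit.

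The cost is wording only: no change to design, recruitment or analysis model. The one thing given up is the possibility of claiming a non-significant trend as support for chat.
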